**Eligibility criteria**

Eligible subjects will be women aged 18 to 45 years who are pregnant with single fetus at gestational age of 20 to 30 weeks and have been diagnosed with type 2 DM or Gestational Diabetes and met the Hospital’s criteria for starting insulin therapy. The criteria for the diagnosis of GDM and DM will be a plasma glucose concentration of greater than or equal to 7 mmol/L after an overnight fast or plasma glucose concentration of equal to or greater than 11.1 mmol/L 2 hours after a 75g glucose drink.^1^

The current criteria for starting insulin therapy in patient with GDM at the diabetes clinic of KBTH are at least one following:

- FBS > 5.1 mmol/l
- 1HPG > 10.0 mmol/L or
- 2HPG > 8.5 mmol/L.

Subjects diagnosed according to the above criteria that are unable to achieve the above targets following management on diet and exercise will be eligible for the study.

**Exclusion criteria**

Exclusion criteria will include patients with insulin dependent Diabetes Mellitus and patients with contraindications to metformin therapy.

SAMPLE SIZE DETERMINATION

Power calculation: The power calculation is based on the difference in 2HPG expected between the metformin and insulin groups at 34 weeks gestation. Using the two sampled mean formula^34^, the estimated sample size was 47 per group. From pre-trial estimates the minimum difference in mean 2HPG levels between the two groups of 4mg/dl (0. 22 mmol/l) is required to give a power of 80% to the study at a significance level of α = 0.05.We recruited 52 in each group to allow for a 10% non-respondent rate

TREATMENT PROTOCOL

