**BACKGROUND**

Diabetes Mellitus is a metabolic disorder of multiple aetiology characterized by, chronic hyperglycaemia with disturbance of carbohydrate, fat and protein metabolism resulting from defects in insulin secretion, insulin action, or both ^1.^  Diabetes Mellitus is broadly grouped into Type I (Insulin Dependent Diabetes Mellitus) and Type II (Non- Insulin Dependent Diabetes Mellitus); the latter is the focus of this study. Diabetes Mellitus in pregnancy consists of pre-gestational Diabetes Mellitus and Gestational Diabetes Mellitus. Gestational Diabetes Mellitus is characterized by hyperglycaemia of varying severity, diagnosed during pregnancy (without previously known diabetes) and usually (but not always) resolving within six weeks of delivery^1^. The prevalence of diabetes mellitus world- wide is projected to increase.^2^

A study in Nigeria estimated the incidence of Diabetes Mellitus (DM) among pregnant women as 1.7%. Pre-gestational diabetes accounted for 39% while Gestational Diabetes was responsible for 61% of cases.^3^ There is no national data on the prevalence of DM among pregnant women in Ghana. Data from Greater Accra estimates the crude prevalence of Diabetes Mellitus as 6.3%^4^. It is estimated that 3-10 % of pregnancies are complicated by Diabetes Mellitus.^5, 6^

Diabetes mellitus is an important complication of pregnancy with adverse effects on both maternal and fetal outcomes. Treatment options of diabetes complicating pregnancy are limited. Several classes of medicines have been developed based on the pathophysiology of diabetes and are being used as monotherapy or combination therapies with varying efficacies in the general population of diabetics. In pregnant diabetics however, exercise and dietary management followed by insulin therapy where dietary management have failed is the general trend. Few countries have added some oral hypoglycaemic agents to this management, but lack of adequate data on efficacy and safety in the pregnant population has slowed this development in several countries.

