**PROBLEM STATEMENT**

Diabetes Mellitus is a common disease in the adult population in both developed and developing countries. In developing countries in particular type 2 diabetes mellitus appears to be on the ascendancy because of life style changes and changing trends in dietary habits. As the disease burden increases in the general population it is expected that its prevalence in pregnancy will also increase. Pregnancies complicated by diabetes mellitus often require specialized care because of adverse maternal and fetal outcome if not properly managed. While several pharmacological options are available to diabetics in the general population for glycaemic control, the pregnant diabetic is often restricted to only insulin following dietary and exercise management failure. Insulin may not be affordable in low income countries. Frequent power outages or the absence of electricity also hinders its use in rural areas. In addition adherence to the frequent injections may be low.

Metformin taken orally is cheaper, more accessible and more user-friendly compared to insulin. Metformin is therefore a logical option for pregnant diabetics in Ghana. Recent clinical trials support metformin use in pregnancy, but lack of such data in Ghana still makes metformin use controversial. Its use during pregnancy has been hampered by lack of data on its efficacy and safety in pregnancy.

Another problem is that the pharmacogenetics of metformin does not support extrapolation of research findings from one place to another since its excretion is influenced significantly by a variant allele. Treatment failure or toxicity could occur in patients carrying the variant allele (*SLC22A2*).^16^

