**AIM**

The aim of this study is to determine if metformin monotherapy or metformin in combination with insulin is more effective at attaining and maintaining glycaemic targets compared to insulin monotherapy in the management of gestational diabetes mellitus and type 2 pre-gestational diabetes mellitus in Ghanaians.

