**Metformin Group**

In the Metformin group, starting dose of Metformin will be 500mg once a day and increased gradually over two (2) weeks, to meet glycaemic targets of FBS < 5.1 mmol/L, 1HPG < 10.0mmol/L and 2HPG < 8.5 mmol/L.

The maximum dose will be 2500mg per day. Insulin will be added if targets cannot be reached on metformin alone at maximum doses. Subjects that receive supplemental insulin will be excluded from the metformin group and analyzed for the purpose of this study as treatment failures. The quantity of supplemental insulin will be documented for analysis.

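### The primary 2HPG comparison pools type 2 and gestational diabetes with no factor for type, while insulin supplementation removes women from the metformin arm only; current metformin use is also not excluded

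*Protocol*

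**What the plan says.** **Population.** The Aim covers "gestational diabetes mellitus and type 2 pre-gestational diabetes mellitus in Ghanaians". Under Eligibility criteria, both diagnoses enter through one gate: women "unable to achieve the above targets following management on diet and exercise will be eligible for the study".

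**Exclusions.** "Exclusion criteria will include patients with insulin dependent Diabetes Mellitus and patients with contraindications to metformin therapy". Nothing is said about metformin already being taken.

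**Allocation.** Study Design uses one ballot in sets of four. It names five matching factors: age, parity, gestation, and weight and glucose profile before treatment. Diabetes type is not one of them.

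**Treatment.** In the metformin arm, "starting dose of Metformin will be 500mg once a day", with a ceiling of 2500 mg a day. Then: "Insulin will be added if targets cannot be reached on metformin alone at maximum doses". And: "Subjects that receive supplemental insulin will be excluded from the metformin group and analyzed for the purpose of this study as treatment failures". Under Insulin group, women who miss targets are admitted and re-titrated, and no removal is stated.

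**Data and analysis.** Data Collection does not list earlier glucose-lowering drugs. Statistical Analysis sets a one-tailed t-test for means and a repeated-measures ANOVA for trends. Neither carries a term for diabetes type.

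**The concern.** The ballot balances diabetes type between the arms in expectation. The later removal of supplemented women acts on one arm only. If type 2 women miss targets on metformin more often and also run a higher 2HPG, the metformin arm loses more of them. Its mean then falls for a reason unrelated to the drug, in the direction that the one-tailed test is looking for. A t-test with no term for type cannot separate this from a treatment effect.

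The secondary issue is who enters. The trial asks about metformin against insulin once diet and exercise have failed. A type 2 woman already above target on metformin is not named in the exclusions. If she drew metformin she would be stepped down to the starting dose. If she then missed targets at the maximum, she would count as a metformin failure and enter the objective on supplemental insulin.

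**Working it through.** **The plan's own figure.** Sample Size Determination gives 47 per group for 4 mg/dl (0.22 mmol/l), 80% power and α = 0.05. No SD is stated, so 47 cannot be reproduced. Solving backwards with the noncentral t, the planned difference is 0.517 SD one-sided (SD 7.7 mg/dl) or 0.584 SD two-sided (SD 6.8 mg/dl). The 52 recruited per group matches 47 × 1.10 = 51.7.

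**Assumed inputs.**
- Type 2 share p = 20–39%. The upper value is the pre-gestational share in the Nigerian study cited in Background; that share is not restricted to type 2.
- Removed from the metformin arm: 40% of type 2 women and 15% of GDM women. The Protocol gives no such rates.
- Gap g in 2HPG between the types: 0.25–0.5 of the overall SD. This is also not in the Protocol.

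**Step 1: type mix after removal.** Share left = p(1 − 0.40) / [p(1 − 0.40) + (1 − p)(1 − 0.15)].
- p = 0.20: 0.12 / 0.80 = 15.0%, a fall of 5.0 points.
- p = 0.39: 0.234 / 0.7525 = 31.1%, a fall of 7.9 points.

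**Step 2: effect on mean 2HPG.** Shift = fall in share × g.
- Low: 0.050 × 0.25 = 0.013 SD; 0.013 / 0.584 = 2% of the planned difference.
- High: 0.079 × 0.5 = 0.040 SD; 0.040 / 0.517 = 8%.

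Against 4 mg/dl, 2–8% is about 0.1–0.3 mg/dl. The shift is zero if both types are removed equally often.

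**Step 3: precision gained from a type factor.** Variance explained r = p(1 − p)g²; reduction in standard error = 1 − √(1 − r).
- p = 0.20, g = 0.25: r = 1.0%, reduction 0.5%.
- p = 0.39, g = 0.5: r = 5.9%, reduction 3.0%.

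**Step 4: what the factor leaves untouched.** Suppose the worst fraction f leaves the metformin arm, there is no true difference, and the correlation between missing target and 2HPG is 0.5 (assumed). The mean shift is −0.5 × φ(c)/(1 − f), where φ is the standard normal density and c cuts off the top f. For f = 10%, 20% and 30% this is −0.10, −0.18 and −0.25 SD. In simulation with 47 per arm, the nominal 5% one-sided error becomes about 12%, 20% and 30%. The removal rule is therefore the larger problem, and a type factor corrects only the part due to type.

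**Step 5: women on metformin at entry.** Suppose k of the 52 women in the metformin arm are such women, each with probability q of needing insulin, over an underlying failure rate f. The observed rate is [f(52 − k) + qk]/52. The Protocol gives none of these values. With f = 20% and q = 50–100%:
- k = 2: 11/52 to 12/52 = 21.2–23.1%.
- k = 5: 11.9/52 to 14.4/52 = 22.9–27.7%.

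**The case against.** **An unadjusted t-test is valid in a randomised trial, and covariates are often left to an SAP.** This is true. A reader might infer that pooling the two types biases the comparison; it does not. At entry, pooling costs only precision. The point stands because the Protocol itself names the test and the one-arm removal, and the removal can undo the balance that the ballot gave. The SAP, if there is one, may already add the factor.

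**The sizes rest on assumption.** This also stands. Only the 39% comes from the document, and it is not a type 2 figure. Eligibility criteria applies one set of diagnostic thresholds to both conditions, so the gap between types may be narrow. Five of 52 women on metformin would mean about 10 of 104 in the trial, or 24–48% of the 21–41 type 2 women implied by a 20–39% share. That is hard to square with the Problem Statement, which calls metformin use in Ghana controversial.

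**The entry text already points to women starting drug treatment.** Largely so. Women must meet the hospital's criteria for starting insulin, and the ballot is for new attenders. The metformin dose is a starting dose. Background says that "exercise and dietary management followed by insulin therapy where dietary management have failed is the general trend", and the Problem Statement says that "the pregnant diabetic is often restricted to only insulin following dietary and exercise management failure". What remains is a wording gap: current metformin use is unlikely but not excluded.

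**A reader might go further and say that such women could not be identified afterwards.** The documents do not support that. Ethical Considerations mentions a questionnaire whose content is not shown, and patient notes are a data source. All that can be said is that prior drugs are not listed under Data Collection.

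**Conclusion.** The point holds as a modest improvement to a stated method. Under the assumptions shown, a type factor would correct a shift of about 0.01–0.04 SD and reduce the standard error by about 0.5–3%. The correction applies only if type 2 women are removed more often and run a higher 2HPG.

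Two stronger inferences fail. Restarting at 500 mg does not make failure automatic, since a woman who came in on a lower dose may reach target on titration. Nor would adjustment for type make the metformin arm comparable again: selection on glucose control within each type remains, and only an analysis of all women as randomised removes it.

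The entry gap is secondary. The number of women affected is unknown and probably small. With two such women the failure rate moves by about 1–3 points from an assumed 20%.

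**What to change.** 1. **Statistical Analysis:** compare 2HPG in a linear model with arm and diabetes type (type 2 versus GDM) in place of the unadjusted t-test. Type is known at entry, so the cost is one model term and one degree of freedom.
2. **Exclusion criteria:** add women taking metformin at screening. A few women become ineligible.
3. **Data Collection:** list glucose-lowering drugs taken before and during the index pregnancy, with dates. The exclusion sets no wash-out, so the dates would show anyone who stopped shortly before entry.

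Leave the diet-and-exercise condition as worded. Adding *alone* could bar previously treated type 2 women, whom the Aim names as a target group. Separate ballots by type are not needed for this gain. The removal rule under Metformin Group needs its own change, to an as-randomised analysis.

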**Treatment failures**

Supplemental insulin for treatment failures in the Metformin group will be prescribed according to the same protocols in the insulin group.

DATA COLLECTION

Basic demographic data will be recorded. They will be followed through their index pregnancy, with 2-weekly blood glucose checks in hospital. All laboratory samples will be collected and analyzed at the diabetes research laboratory by staff of the same laboratory. Venous blood will be used for blood glucose profile analysis. Analysis of Fasting Blood Glucose (FBG), one- hour post-prandial glucose (1HPG), two- hour post-prandial glucose (2HPG) will be done using the Mindray BS-400^®^ (Mindray Medical Int. Ltd, China) chemistry analyzer. The method for glucose determination will be enzymatic photometric testing. Urinalysis, weight records (using Seca^®^(gmbh&Co. Kg Germany)) and cost of treatment will also be documented. The optimal dose of metformin required for optimal glycaemic control will be recorded for each patient. Peri-partum events like gestational age at delivery, type of delivery, fetal birth weight, and NICU admissions will be retrieved from patient notes.

STATISTICAL ANALYSIS

In analyzing the data, summary statistics will include appropriate tables and charts. Categorical data will be represented by pie and bar graphs and continuous data with histograms.

For inferential statistics, significant difference of mean observations using one-tail student’s t-test and z-score for differences in proportions where applicable. The differences in trends of glycaemic profile over time between the study groups will be assessed by two-way repeated measures analysis of variance (ANOVA).

Significance level (p-value) will be set at α = 0.05. Data analysis will be done using statistical package for social science **(SPSS** version 20).

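### The 80% power claim for a 0.22 mmol/L difference in 2HPG rests on an unstated SD of about 0.4 mmol/L, and the sample size makes no allowance for removing metformin failures

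*Protocol*

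**What the plan says.** The Protocol, under Sample size determination, bases the calculation on the difference in 2HPG between the metformin and insulin groups at 34 weeks. "Using the two sampled mean formula", it arrives at 47 per group. It cites pre-trial estimates and states that a "minimum difference in mean 2HPG levels between the two groups of 4mg/dl (0. 22 mmol/l) is required to give a power of 80" per cent, "to the study at a significance level of α = 0.05". It then adds: "We recruited 52 in each group to allow for a 10% non-respondent rate". No SD appears there or anywhere else in the Protocol. Sidedness is not given in that section, but Statistical analysis plans a test for "significant difference of mean observations using one-tail" Student's t.

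Under Metformin Group the Protocol says: "Subjects that receive supplemental insulin will be excluded from the metformin group". These women are to be analysed as treatment failures. No expected failure rate is given.

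The Expected outcome section names the difference in 2HPG as the primary outcome.

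**The concern.** The SD is an essential input to a two-sample means calculation. Without it, a reader cannot check whether 47 per group delivers 80% power. The difference chosen is small on the scale of the Protocol's own glucose thresholds, so a sample of 47 needs a very narrow spread of 2HPG to work. The population does not suggest a narrow spread: it combines type 2 and gestational diabetes, in-patients and out-patients, and women whose glucose was not controlled on diet and exercise.

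The number analysed is a separate problem. The only inflation is for non-response, yet the plan also takes women out of one arm for a reason it foresees, since supplemental insulin in the metformin group is itself one of the Specific objectives.

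At stake is how the primary result is read. The first hypothesis is that metformin is equally effective. If true power is far below 80%, a non-significant difference could be taken as support for that hypothesis when the trial had little chance of detecting 0.22 mmol/L. The Protocol also expects that the findings may inform policy on the level of care at which these women are managed.

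**Working it through.** **Inputs from the Protocol.** Difference 4 mg/dl = 0.22 mmol/L (4/18.016 = 0.222, so the conversion is right); power 80%; α = 0.05; one-tailed t-test (Statistical analysis); 47 per group; equal groups; 52 recruited per group. The SD is not given, so 47 cannot be reproduced forward and has to be solved backward.

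**Step 1: the SD that 47 per group implies.** From n = 2(z₁₋α + z₁₋β)²·SD²/δ², SD = δ / [(z₁₋α + z₁₋β)·√(2/n)], with √(2/47) = 0.2063.

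- One-sided: 0.22 / (2.486 × 0.2063) = 0.429 mmol/L. The non-central t gives a standardised effect of 0.517, so SD = 0.22/0.517 = 0.426 mmol/L (about 7.7 mg/dl).
- Two-sided: 0.22 / (2.802 × 0.2063) = 0.381 mmol/L. The non-central t gives 0.584, so SD = 0.22/0.584 = 0.377 mmol/L (about 6.8 mg/dl).

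The implied SD is therefore about 0.4 mmol/L under either formula and either sidedness. With roughly normal data, about 95% of women would lie within 1.96 × 0.426 = 0.83 mmol/L of their group mean (0.74 mmol/L for the two-sided value).

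**Step 2: sensitivity to the SD.** The SDs below are assumptions, because the documents give none. Power is for 0.22 mmol/L with 47 per group (non-central t). The detectable difference at 80% power is 0.517 × SD one-sided or 0.584 × SD two-sided.

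| Assumed SD (mmol/L) | Power, one-sided | Power, two-sided | Detectable difference, one-sided (mmol/L) | Detectable difference, two-sided (mmol/L) |
|---|---|---|---|---|
| 0.5 | 68% | 56% | 0.26 | 0.29 |
| 1.0 | 28% | 18% | 0.52 | 0.58 |
| 1.5 | 17% | 11% | 0.78 | 0.88 |
| 2.0 | 13% | 8% | 1.03 | 1.17 |

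Analysing all 52 per group changes little: at an SD of 1.0 mmol/L, one-sided power is 30%.

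**Step 3: the failure rule.** The 10% allowance leaves 52 × 0.9 = 46.8 per group, which is the required 47 with nothing to spare. Let f be the share of metformin women removed because they received supplemental insulin. The table takes the SD at its implied one-sided value of 0.426 mmol/L and uses the one-sided non-central t with unequal arms.

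| f (assumed) | Allowance used up: 47(1−f) vs 47 | No non-response: 52(1−f) vs 52 |
|---|---|---|
| 10% | 78% | 82% |
| 20% | 76% | 79% |
| 30% | 73% | 77% |

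If all 52 per group are otherwise retained, power stays at or above 80% until about 17% of the metformin arm has been removed.

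**The case against.** The strongest reply is that nothing stated is miscalculated. The unit conversion is right, 47 to 52 is within rounding of a 10% allowance, and the calculation rests on pre-trial estimates that may contain an SD near 0.4 mmol/L. This stands as far as it goes: the 80% is unsupported, not refuted.

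A reader might go further and infer that an SD of 0.4 contradicts the Protocol's own text. The documents do not support that.

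- The criterion "plasma glucose concentration of equal to or greater than 11.1 mmol/L 2 hours after a 75g glucose drink" is a diagnostic threshold after a glucose load and an alternative to a fasting criterion. It does not describe on-treatment 2HPG at 34 weeks.
- Provision for failures and re-admissions does not imply a wide 2HPG spread. The Protocol sets three targets, and a woman may miss the fasting or 1-hour target while meeting the 2-hour one.
- Any figure for the share of women above 8.5 mmol/L depends on a mean that the Protocol does not give.
- Removing failures might itself narrow the spread among those left.

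A reader might also infer that the 80% holds only if no metformin woman is removed. That is too strict. Removing 10% of 47 costs about 2 points, and unused non-response allowance absorbs more.

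Finally, sidedness is not wholly absent, since Statistical analysis specifies a one-tailed test. That is why the one-sided figures are the main ones here, and they do not rescue the claim at the larger SDs.

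**Conclusion.** The point holds in this form: the power stated for the primary outcome depends on an unstated and very small SD, about 0.43 mmol/L one-sided or 0.38 mmol/L two-sided, which the Protocol neither gives nor justifies. The result is highly sensitive to it. Going from the implied SD to 1.0 mmol/L takes one-sided power from 80% to 28%. That such a small SD is implausible in this mixed population is a judgement; the documents contain no 34-week distribution that would settle it.

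The missing allowance for the failure rule is real but secondary. Within the assumed range of 10% to 30% removed, it costs about 2 to 7 points if non-response uses up the allowance, and less otherwise. The true loss is unknown because no failure rate is stated.

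**What to change.** Keep 52 per group and amend the sample size section as follows.

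1. State the SD, its source in the pre-trial data, and the sidedness used to reach 47.
2. Replace the single power figure with a short table of power and detectable difference over a realistic SD range, such as 0.5 to 2.0 mmol/L, informed by the clinic's own 2HPG records.
3. Compute and run the primary 2HPG comparison on all randomised women in their assigned group, and report supplemental insulin as a separate failure outcome. No further loss of numbers then arises from the failure rule. It also agrees with the Aim, which includes metformin combined with insulin in the comparison.
4. Withdraw the claim of 80% power for 0.22 mmol/L unless the pre-trial data show an SD near 0.4 mmol/L.

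This costs some redrafting and needs no extra patients. The downside is that the stated power will probably become less favourable.
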